**CHARACTERISTICS OF THE SUBJECT POPULATION (3-9)**

**3. Accrual**

**a. What is the maximum number of subjects that will be consented at UNMC, The Nebraska Medical Center or other sites approved by the UNMC IRB (that is, sites listed in Section I of this application)?** 180

**b. What is the statistical or other justification for the maximum accrual requested?**

A detailed analysis of the statistical power and sample size requirements of this study was prepared by [name] in July 2005, and is attached to this 5-year re-write in fulfillment of the requirements of this section. This statistical power and sample size analysis concludes that the study goals can be met with a total enrollment of 200 subjects, which is sufficient to compensate for a 10% drop-out rate. Our experience with this study to date appears to substantiate this enrollment size as being appropriate to meet study goals.

**c. For multicenter protocols, what is the total number of subjects to be enrolled at all sites?** NA – this is a single-center protocol.

**4. Gender of the Subjects**

**a. Are there any enrollment restrictions based on gender?**

No, both male and female subjects are eligible for enrollment.

**b. Are there any enrollment restrictions based on child-bearing potential?**

All sexually active kidney recipients of childbearing potential are strongly encouraged to use two reliable, medically acceptable forms of birth control prior to and following kidney transplantation while actively on immunosuppressant drugs. The side effects of these drugs on developing fetuses make this necessary. Female study participants who are not of reproductive potential (have reached menopause or undergone hysterectomy, oophorectomy, or tubal ligation) or whose male partner has undergone successful vasectomy with resulting azoospermia or has azoospermia for any other reason, are eligible without requiring the use of contraception. Male study volunteers, who have undergone successful vasectomy with resulting azoospermia or have azoospermia for any other reason, are eligible without requiring the use of contraception**.**

**c. Are there any specific contraception requirements?**

Two reliable, medically acceptable forms of birth control should be used prior to and following kidney transplantation while an individual of childbearing potential is actively on immunosuppressant drugs.

**d. Are pregnant or breast feeding women excluded from participation?**

As is standard of care for transplantation recipients, pregnant women may not participate in this study due to the potential teratogenic effects of immunosuppressant on developing fetuses.

**5. Age Range of Subjects**

**a. What is the age range of the adult subjects?**

Subjects will be between 19 and 65 years of age.

**b. What is the rationale for selecting this age range?**

Adults greater than 65 years of age are at an increased risk for the following complications surrounding transplantation and immunosuppressive therapy:

- Death due to cardiovascular disease
- Prolonged surgical recovery
- Infection and malignancy related to immunosuppression
- Slowed metabolism of immunosuppressive drugs
- Decline in cognitive function which may lead to inability to comply with post-transplant care.

Specific to this study, patients greater than 65 years of age may not be able to tolerate a single dose of rATG due to the propensity for decreased cardiac function.

The lower age limit was selected because in Nebraska the age of majority is 19 years old.

**c. Will children and/or adolescents (18 years of age or younger) be included in this research?**

No children and/or adolescents will be included in this research. The medications utilized in this study have not been well studied in children less than 18 years of age, resulting in a concern about the potential for a negative impact on development or unforeseen side effects.

**6. Race and Ethnicity**

**Are there any subject enrollment restrictions based upon race or ethnic origin?**  There are no enrollment restrictions based upon race or ethnic origin.

**7. Vulnerable Subjects**

**Will any of the following populations be specifically recruited for enrollment in this research?**

**a. Prisoners**

**b. Pregnant women or fetuses**

**c. Cognitively or decisionally impaired**

**d. Economically or socially disadvantaged**

**e. Terminally ill**

No vulnerable subjects will be enrolled in this study.

**8. Inclusion Criteria**

**What are the specific inclusion criteria?**

- 1. Primary renal transplant recipient
  2. Recipient of a re-transplant, if:
- previous graft(s) lost due to non–immunological factors, ***or***
- previous graft(s) lost due to immunological factors, but while maintained on the less-effective immunosuppression agents of the previous era, i.e., cyclosporine, steroids, and/or azathioprine
  1. Cadaveric donors
  2. Living renal donor
  3. Recipient of renal transplant with planned pancreas transplant at a later date
  4. Zero-mismatch human leukocyte antigen donors

**9.** **Exclusion Criteria**

**What are the specific exclusion criteria?**

1. Recipient age <19 years or >65 years
2. Previous history of CMV disease
3. Hepatitis B and C recipients
4. Primary disease states that require steroids for immunosuppression
5. Re-transplant with immunological cause of renal or pancreas loss
6. Non-heart beating donors
7. Recipient of pediatric en bloc kidneys
8. Recipient with a PRA >75%
9. Patients who have received 3 or more prior transplants, excluding pancreas
10. Patients who are past recipients of other solid organ transplants
11. Previous history of BK virus
12. Previous treatment with rATG
13. Allergy to rabbits
14. Simultaneous Kidney/Pancreas transplantation

**METHODS AND PROCEDURES (10-12)**

**10. Methods and Procedures Applied to Human Subjects**

a. Briefly describe the study design (e.g. randomized, double blind, cross-over, phase III).

This is a prospective, randomized, non-blinded 2 x 2 factorial comparison of clinical outcomes in 180 renal transplant recipients receiving either a single dose of rATG at 6 mg/kg or 4 doses given every other day at 1.5 mg/kg/dose. Immediately after renal transplantation, each of these groups will undergo our clinically-standard early steroid withdrawal; approximately 6 months later, half the subjects in each group will be switched to maintenance immunosuppression using Sirolimus/MMF.

**b. Are there any tests performed prior to signing of the consent form in order to determine eligibility for this research protocol?** No.

**c. Describe sequentially all procedures, interventions and evaluations to be applied to subjects, and identify any that are experimental or performed exclusively for research purposes.**

Participants must sign a written consent form prior to initiation of any study procedure.

At the time of transplantation, the participant will be randomized to one of 4 groups: (1) single-dose rATG at 6 mg/kg plus rapamycin and tacrolimus maintenance immunosuppression, (2) divided-dose (4 doses) rATG given every other day at 1.5 mg/kg/dose plus rapamycin and tacrolimus maintenance, (3) single-dose rATG plus rapamycin and tacrolimus maintenance with conversion after 6 months to rapamycin and mycophenolate mofetil maintenance, and (4) divided-dose rATG plus rapamycin and tacrolimus maintenance with conversion after 6 months to rapamycin and mycophenolate mofetil maintenance. Given the long-term effects of rATG, single-dose versus divided-dose administration may have a differential impact on the patient’s requirements for maintenance immunosuppression (see section II.2). For this reason, we are randomizing patients to the 4 treatment groups delineated above.

Participants will receive all standard post-transplant clinical care and follow-up. This includes receiving both tacrolimus and rapamycin for the first 6 months post-transplantation. At the month 6 time point, the investigator will determine if it is safe for those subjects in groups 3 and 4 to transition to rapamycin and mycophenolate mofetil for maintenance immunotherapy. Eligible subjects will have had no rejection episodes in the first six months and will be able to tolerate a dose of rapamycin that achieves a trough level of no less than 8 ng/ml.

Participants will have renal function determined by estimated glomerular filtration rate (GFR) calculated according to the formula currently recommended by the National Kidney Foundation^6,7,8^. These GFR assessments will be made daily during the first one to three weeks post-transplantation, becoming monthly thereafter. 24-hour urine creatinine clearance at 1, 3, 6, 12, and 24 months may also be used to assess graft function. The creatinine clearance test is standard practice. There are a number of factors which can affect the accuracy of the 24 hour urine collection, such as misinterpretation of the instructions provided to patients regarding method of collection; temperatures at which the samples are maintained; and a voiding that is not collected, thus yielding an altered result. The calculated GFR will provide an accepted, objective measure for comparison among the groups.

Participants will undergo assessment of several immunologic parameters to assess potential mechanisms of action of each of these dosing regimens. Each of the parameters will be tested from peripheral blood samples obtained during routine clinical visits.

To measure the long-term effect of rATG, CD3 and CD4/CD8 counts with ratio will be done at baseline, two weeks post transplant, 1, 3, 6, 12, and 18 months, and annually to year 5. These tests are performed for research purposes.

Participants may be asked to have this additional blood drawn in order to test for certain immunological parameters. This will depend on whether or not the patient is able to return to the transplant center at the required intervals. The investigator, in consultation with the patient and the study coordinator, will determine if this is possible.

The following blood tests will be performed to determine if T-cells are being re-educated in the thymus following rATG administration:

- Transglutaminase expression will be measured 1 hr post-initiation of first dose of rATG.

● Serum levels of ε (γ-glutamyl)-lysine diisopeptide will be measured every other day for 7 days post-transplantation then weekly until pre-transplant levels are reached.

● TREC output will be measured weekly, until levels return to baseline, beginning 2 days post-completion of rATG therapy.

● CD3 counts will be measured daily until total counts are > 100.

● Gene array analyses for assessment of functional signal transduction pathways and analysis of cell surface phenotypes of peripheral blood leukocytes will be performed at 1, 3, 6, and 12 months post-transplantation.

All participants will follow the standard post-transplant schedule for routine laboratory testing.

For safety purposes, subjects will have surveillance biopsies at 6, 12, and 24 months. If future funding becomes available, a renal biopsy at year 5 may be added. (If this becomes feasible, the protocol will be amended and an addendum consent form will be prepared for the subjects.) Subjects who present with a condition, either medically or anatomically, that would present a greater risk to the subject, may at the discretion of the Principal Investigator forego a kidney biopsy. Banff scoring will be utilized to categorize rejection and transplant nephropathy. It is standard practice at this center to request surveillance biopsies for renal transplant recipients who are not receiving steroids as part of their maintenance immunosuppression.

Participants will return for study visits at 1, 3, 6, 12, and 24 months and as needed in accordance with standard schedule for all transplant patients. Long-term data regarding graft and patient survival, incidence of allograft rejection, serious adverse events, CMV disease, opportunistic infections, PTLD, hyperlipidemia, wound healing problems, lymphoceles and immunosuppression regimen will be collected at years 3, 4, and 5 from a review of the subject’s medical record.

Adverse Events:

All adverse events will be monitored and recorded. These will include both events related to the safety profile of the study drugs (CMV disease, Post-Transplant Lymphoproliferative Disorder [PTLD], opportunistic infections, elevated lipids, etc.) and expected renal transplant complications (wounds, lymphoceles, diabetes, weight gain, etc.). All unexpected adverse events and any deaths will be reported to the IRB per UNMC policies.

Endpoints:

Primary endpoints:

1. Cumulative calcineurin nephrotoxicity/ transplant nephropathy per clinically-indicated and protocol surveillance biopsies (Banff grading criteria)
2. Renal function by either measured 24-hour urine creatinine clearance at 1, 3, 6, 12 and 24 months or calculated GFR (Glomerular Filtration Rate) by using the abbreviated MDRD (aMDRD) formula and patient serum creatinine and demographic data. This may be calculated from routine blood draws, allowing multiple data points to be collected within each month.

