**15. Data and Safety Monitoring**

**a. How will subject safety be assessed on an ongoing basis throughout the study?**

All subjects will be scheduled for follow up visits as outlined previously, which is standard practice in renal transplant. Investigators and participating healthcare providers will be present at the follow-up visits. Additionally, post-transplant coordinators will be following subjects, as is standard practice, through phone calls and other communications. Laboratory tests and biopsies performed at the various visits throughout the study will also allow for assessment of subject safety.

**b. What specific procedures will be utilized to prevent or minimize potential risks or discomforts associated with study interventions and procedures?** Thymoglobulin^®^; Prograf^®^; Rapamune^®^: CellCept^®^. Participants will be monitored closely for infections, malignancies, and any other adverse reactions.

Kidney biopsies: Precautions typically taken to minimize the risks of a biopsy include obtaining the following tests prior to the biopsy: a complete blood count, coagulation factors, renal ultrasound, and urinalysis. In addition, the biopsy is performed under the guidance of ultrasound.

To prevent bleeding at the site after the biopsy, patients are required to remain in bed for 6 hours and to lay for 4 hours following the procedure. A 5 lb. sandbag is placed over the site. Patients are closely observed and vital signs are checked regularly during this time.

Drawing blood: All usual precautions will be taken.

Randomization: All groups of subjects will receive standard maintenance therapy of tacrolimus and rapamycin in the early post-transplant period (i.e. to month 6). Only those randomized to groups 3 and 4 who have not experienced rejection and who are able to maintain rapamycin trough levels of 8 ng/ml or greater, will be transitioned to rapamycin and mycophenolate mofetil.

Pregnancy: All sexually active participants are required to practice two methods of medically acceptable birth control as long as they are on study medication and for 3 months following the discontinuation of study medication. For female subjects, pregnancy tests will be done prior to start of study medication, and if a pregnancy occurs, the participant will be withdrawn from the study.

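### The maintenance arm is assigned at transplantation in an open trial, about six months before it is used, and nothing withholds it during the shared treatment phase

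*Protocol*

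**What the plan says.** Protocol item 10a describes the design: "This is a prospective, randomized, non-blinded 2 x 2 factorial comparison of clinical outcomes in 180 renal transplant recipients". Of the maintenance factor it says that "approximately 6 months later, half the subjects in each group will be switched to maintenance immunosuppression using Sirolimus/MMF".

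Item 10c sets the time of allocation: "At the time of transplantation, the participant will be randomized to one of 4 groups". Groups 1 and 2 (single and divided rATG) stay on tacrolimus and rapamycin. Groups 3 and 4 (single and divided rATG) convert to rapamycin and mycophenolate mofetil after six months. One draw therefore settles both factors. The abstract gives the ratio as 1:1:1:1.

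Until conversion the regimen is common to all. Item 10c says of standard care that "This includes receiving both tacrolimus and rapamycin for the first 6 months post-transplantation", and the abstract and item 15b agree.

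At month 6, "the investigator will determine if it is safe for those subjects in groups 3 and 4 to transition to rapamycin and mycophenolate mofetil". The criteria come from the preceding six months: "Eligible subjects will have had no rejection episodes in the first six months and will be able to tolerate a dose of rapamycin". The trough on that dose must be at least 8 ng/ml. Item 15b restates both criteria, with the same 8 ng/ml threshold, for the same two groups: "Only those randomized to groups 3 and 4 who have not experienced rejection and who are able to maintain rapamycin trough levels".

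The first primary endpoint in item 10c is cumulative nephropathy, counting both clinically indicated and surveillance biopsies. The second is renal function, with creatinine clearance scheduled at months 1, 3, 6, 12 and 24, or calculated GFR as the alternative.

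**The concern.** Only the rATG half of the assignment is needed on the day of surgery. If the maintenance half is visible from that day, clinicians and subjects know for about six months who is due to lose tacrolimus. Three features of this protocol make that relevant.

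- The conversion criteria (no rejection, adequate rapamycin trough) are produced by care in the shared phase and are described only for Groups 3 and 4. Someone who knows the group has a reason to manage rapamycin, or to pursue a suspected rejection, differently.
- The cumulative nephropathy endpoint counts biopsies prompted by clinical judgement, so biopsy intensity before month 6 enters a primary endpoint.
- The background (item 2) records concern about rejection when calcineurin inhibitors are removed. Closer watching of subjects due for withdrawal is therefore foreseeable.

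At stake is the second primary goal, the comparison of converted with continued maintenance. Groups 1+2 and 3+4 should arrive at month 6 differing only by chance. Early disclosure removes the design's guarantee of that.

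**Working it through.** This is a question of timing and disclosure, so most of the check is reading. The arithmetic only sets bounds.

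**1. Is the maintenance arm fixed at month 0?** Yes. Item 10c describes one draw to four groups, and the group definitions contain the conversion. No second randomisation is described.

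**2. Is it withheld until month 6?** No section says so. The trial is declared non-blinded and the group label carries the maintenance arm. That the arm is known is an inference, though a natural one; no section says who holds the list or what subjects are told.

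**3. Does the stated reason require disclosure at month 0?** Item 10c explains the four groups by a possible effect of induction on maintenance needs. That supports crossing the two factors. It does not bear on when the second is released.

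**4. Which comparison is exposed?** With 180 subjects at 1:1:1:1 there are 180/4 = 45 per group and 180/2 = 90 per maintenance arm. Each induction arm contains equal numbers due to continue and to convert, so steering by future maintenance arm should roughly balance between single and divided rATG. The exposure is mainly in the maintenance comparison.

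**5. How large could it be?** The protocol gives no figure for differential care before month 6. Two illustrations follow, both on assumed inputs.

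- *Biopsy ascertainment.* Assume that knowledge of the future arm changes the biopsy rate by 5 to 15 percentage points and that 30% of biopsies show a countable finding. The spurious difference is 0.05 × 0.30 = 0.015 to 0.15 × 0.30 = 0.045, or 1.5 to 4.5 points. For cumulative nephropathy this probably overstates the effect, because a persistent lesion would often be found at the scheduled month-6 biopsy anyway.
- *Shift in a continuous outcome.* Assume a pure bias of d standard deviations between 90 and 90 subjects, no true effect, and a two-sided 5% test. The standardised shift is d × √(90/2) = d × 6.71. The chance of rejection is P(Z > 1.96 − 6.71d) + P(Z < −1.96 − 6.71d).

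| Assumed d | 6.71d | Chance of rejection |
|---|---|---|
| 0 | 0 | 5% |
| 0.1 | 0.67 | 10% |
| 0.2 | 1.34 | 27% |
| 0.3 | 2.01 | 52% |

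Nothing in the protocol says which row applies, or in which direction.

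**6. How many subjects can a change still reach?** Item 19b reports an analysis of 142 patients. Item 3a caps accrual at 180, and item 10a uses the same number. So 180 − 142 = 38, and 38/180 = 21%. This is an upper bound, since others may have been randomised since. (Item 3b names 200, which equals 180/0.90. The bound here uses the 180 cap.)

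**The case against.** The strongest reply is that one up-front allocation to four cells is an ordinary way to run a 2 × 2 factorial trial, openly declared here, and that no contradiction is shown. That stands: this is an avoidable weakness of the design, not an error in the text.

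The protocol also has real safeguards. All groups receive standard care on the same two drugs to month 6, a surveillance biopsy is scheduled for everyone at month 6, biopsies are scored by Banff criteria, and calculated GFR is an objective measure. These limit the problem. They do not govern who has an extra biopsy or how rapamycin is adjusted.

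Several stronger readings are tempting, and the document does not support them.

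- *That one unblinded team orders the biopsies, reads them and diagnoses rejection.* The protocol names neither who orders clinically indicated biopsies nor who reads them.
- *That the investigator may waive biopsies freely.* The phrase "may at the discretion of the Principal Investigator forego a kidney biopsy" applies to subjects whose medical or anatomical condition would put them at greater risk. It concerns surveillance biopsies, of which only the month-6 one touches the shared phase.
- *That analysis cannot help.* Renal function and biopsy status at month 6 precede conversion, so adjusting for the month-6 value can reduce carry-over. It would not repair differential drop-out or differing biopsy intensity.
- *That the induction comparison is equally affected.* The crossing largely protects it.

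A further fair point is that a late change leaves two disclosure regimes in one trial.

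**Conclusion.** The point holds as a possible bias. The maintenance arm is assigned about six months before use in an open trial, nothing withholds it, and the conversion criteria and a primary endpoint both depend on care in that interval. The conclusion rests on one inference, that an assignment neither blinded nor withheld is known to those giving care.

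Size and direction are unknown. The 1.5 to 4.5 points and the 10% to 52% false-positive rates follow from assumed inputs and are not estimates for this trial. A reader might infer that care was in fact steered; the protocol contains no evidence of that.

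The matter mainly concerns the continuation-versus-withdrawal comparison. The remedy is a cheap improvement with limited reach: at most about 38 of 180 subjects for the change in disclosure, and all subjects for the reporting and sensitivity checks. Those checks can still be specified in advance, because item 15e leaves the timing of the formal withdrawal analysis open.

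**What to change.** **Subjects not yet randomised.** Keep the existing 1:1:1:1 list and release it in two steps. At transplantation, disclose only single or divided rATG. Whoever holds the list discloses the maintenance assignment after that subject's month-6 visit and biopsy data are recorded. No dose, conversion criterion or visit changes.

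**Subjects already randomised.**

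- State in the protocol, and later in the report, that the maintenance assignment was made at transplantation in an open trial.
- Compare Groups 1+2 with Groups 3+4 on events before month 6: biopsies performed, rejection diagnoses, rapamycin troughs and drop-out. A lack of difference would be reassuring but would not prove the absence of bias.
- For the maintenance comparison, add a sensitivity analysis of renal function after month 6 adjusted for the month-6 value. It should not be used for the induction comparison, where the month-6 value is itself an outcome.

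**Cost.** A short amendment and a two-step release, with no added subjects, visits or procedures. Subjects and staff learn the maintenance arm later. The trial will contain two disclosure regimes, so the regime should be recorded for each subject. The gain is limited because accrual is largely complete.

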**PURPOSE OF THE STUDY AND THE BACKGROUND (1-2).**

**1. Purpose of the Study**

**What are the specific scientific objectives (aims) of the research?**

Primary goals:

1. Compare the safety and efficacy of single-dose (6 mg/kg) rATG induction with the same total dose (6 mg/kg) administered every other day for four doses (divided-dose).
2. Compare standard renal transplantation outcome measures in patients converted approximately 6 months post-transplantation from maintenance immunosuppression with sirolimus and tacrolimus to sirolimus and low-dose mycophenolate mofetil.

Secondary goals:

1. Determine the immunological consequences of single-dose (6 mg/kg) versus divided-dose administration of rATG
2. Determine the immunological consequences of calcineurin-inhibitor (CNI) continuation versus CNI withdrawal.
3. Perform a cost analysis of single-dose vs. divided-dose administration of rATG.

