**e. Describe briefly the statistical methods used to analyze the data.**

Binomial and numerical outcomes are described using proportions and means, respectively, and are compared using chi-square test or Fisher’s exact test when appropriate and t test, respectively. Graft survival and acute rejection rates are determined using Kaplan-Meier estimates and are compared using log-rank tests. The effects of covariates on the hazard risk of graft survival and acute rejection are evaluated using a Cox proportional hazard model.

A mixed-model for repeated measures is used to compare calculated GFR values to examine the effect of single versus divided-dose rATG on kidney function. A linear mixed-model of repeated measures is used to examine the relationship between the amount of rATG infused at the time of reperfusion and calculated GFR during the follow-up period.

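### For the withdrawal comparison, the cumulative nephropathy endpoint has no month-6 reset, so it counts lesions that arose while all groups were on the same drugs

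*Protocol*

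**What the plan says.** The protocol runs two treatment contrasts that start at different times. On allocation, item 10c says "At the time of transplantation, the participant will be randomized to one of 4 groups". Induction differs from that day. Maintenance does not: "This includes receiving both tacrolimus and rapamycin for the first 6 months post-transplantation". Groups 3 and 4 may then change regimen if they have had no rejection and tolerate the required sirolimus trough; Groups 1 and 2 continue.

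Primary goal 2 (item 1) is to "Compare standard renal transplantation outcome measures in patients converted approximately 6 months post-transplantation". It sets no time window.

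One list of endpoints serves both primary goals. Endpoint 1 is "Cumulative calcineurin nephrotoxicity/ transplant nephropathy per clinically-indicated and protocol surveillance biopsies", by Banff criteria. On the biopsy schedule, item 10c says: "For safety purposes, subjects will have surveillance biopsies at 6, 12, and 24 months". Endpoint 2 is renal function by "measured 24-hour urine creatinine clearance at 1, 3, 6, 12 and 24 months or calculated GFR". Acute rejection and graft survival are secondary endpoints.

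Item 10e gives t tests, chi-square or Fisher tests, and, for time-to-event outcomes, "Graft survival and acute rejection rates are determined using Kaplan-Meier estimates and are compared using log-rank tests". It adds a Cox model with unnamed covariates for those two outcomes. Its GFR mixed models address rATG dosing only. Item 15e mentions a separate formal analysis of the withdrawal phase and leaves its timing open.

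**The concern.** For Groups 3+4 versus 1+2, the first six months are a shared run-in. Nothing that happens in that period can be an effect of withdrawal. An endpoint that accumulates lesions from every biopsy, including for-cause biopsies before month 6 and the month-6 surveillance biopsy, adds the same expected amount to both sides. It therefore pulls the difference towards zero.

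The same would happen to renal function if early values were pooled with later ones, and to rejection if follow-up for this contrast began at transplant. The stake is sensitivity on a primary goal: a real reduction in calcineurin-inhibitor injury, or a real increase in rejection, becomes harder to see. The month-6 biopsy and renal function scheduled in all groups could serve as a baseline, but no section gives them that role for goal 2.

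**Working it through.** The protocol gives no lesion rate, effect size or power figure for this contrast, and its power analysis is an attachment that is not shown. There is no stated figure to reproduce, so everything below is illustration.

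**Inputs from the protocol.** 180 subjects in a 2 x 2 factorial (item 10a), so 180/2 = 90 per maintenance strategy. Renal function at months 1, 3, 6, 12 and 24. Calculated GFR daily for one to three weeks, then monthly.

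**Assumed inputs.** Two-sided alpha 0.05; new lesions after month 6 in 30% (continuation) and 15% (withdrawal); shared prevalence b at month 6 of 10, 20 or 30%.

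**1. Nephropathy, treated as yes/no.** Cumulative risk = b + (1 − b)p, so the difference is (1 − b) × 15 points. Power = Φ(difference/SE − 1.96), with SE = √{[p₁(1 − p₁) + p₂(1 − p₂)]/n}. For the cumulative endpoint n = 90. For new lesions among those lesion-free at month 6, n = 90(1 − b).

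| b | Cumulative risks | Difference | Power, cumulative | Power, new lesions |
|---|---|---|---|---|
| 10% | 37.0% v 23.5% | 13.5 | 51% | 64% (n = 81) |
| 20% | 44.0% v 32.0% | 12.0 | 39% | 59% (n = 72) |
| 30% | 51.0% v 40.5% | 10.5 | 30% | 54% (n = 63) |

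For b = 10%: SE = √[(0.37 × 0.63 + 0.235 × 0.765)/90] = 0.0677; 0.135/0.0677 = 1.99; Φ(0.03) = 51%. A pooled-variance test gives 50/38/29% and 63/58/52%.

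**2. Renal function, only if early values are pooled.** Two of the five scheduled times follow month 6, so an unweighted mean keeps 2/5 = 40% of a post-conversion difference. With all calculated values to month 24, the share after month 6 is 18/(7 + 6 + 18) = 58% down to 18/(21 + 6 + 18) = 40%.

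Assume a difference of 8, SD 18 and equal correlation 0.5 between visits:
- Mean of five visits: SD = 18√[(1 + 4 × 0.5)/5] = 13.94; SE = 13.94√(2/90) = 2.08; 3.2/2.08 = 1.54; power 34%.
- Mean of months 12 and 24: SD = 18√(1.5/2) = 15.59; SE = 2.32; 8/2.32 = 3.44; power 93%.
- The same mean adjusted for month 6: SD = 18√(0.75 − 0.25) = 12.73; SE = 1.90; 8/1.90 = 4.22; power 99%.

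**3. Rejection, only if counted from transplant.** Assume 40 events, a hazard ratio of 2.0 after conversion, and a fraction f of events before month 6. The average hazard ratio is about 2^(1 − f). Power ≈ Φ(log HR × √D/2 − 1.96), with D = 40 from transplant and D = 40(1 − f) from month 6.

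| f | Average HR | Power from transplant | Power from month 6 |
|---|---|---|---|
| 25% | 1.68 | 38% | 48% |
| 50% | 1.41 | 19% | 34% |
| 75% | 1.19 | 8% | 19% |

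**The case against.** A reader might infer that every goal-2 endpoint is analysed from transplant. The text does not say so. The Kaplan-Meier sentence gives no origin, no withdrawal analysis of GFR is specified, item 15e separates the withdrawal phase from the induction phase, and item 19b already reports a nephropathy rate at month 6 for the induction comparison. A statistical analysis plan could supply the origin and the baseline. This stands for rejection and GFR. It does not rescue endpoint 1, whose cumulative wording is in the protocol itself.

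Months 1, 3 and 6 properly serve the rATG goal, and collecting them dilutes nothing. A comparison at months 12 and 24 avoids the loss. This stands.

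A reader might also infer that existing lesions will be charged to withdrawal because no text orders the biopsy before conversion. That is weak. Item 10c has the investigator judge safety at month 6, requires freedom from rejection, and schedules the biopsy for safety, which together suggest biopsy first. Shared lesions also dilute the contrast; they do not fall on one arm. Nor does the protocol say that a null result would be read as equivalence: goal 2 only compares.

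The rates are assumed, and a graded Banff analysis need not shrink as the yes/no calculation does. This stands.

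Finally, analysis from randomisation is valid and conservative. In an open-label trial, allocation is known throughout the run-in and could affect management before month 6, so restricting to lesion-free subjects conditions on post-randomisation status. This argues for adjusting rather than restricting, and for keeping a from-transplant sensitivity analysis.

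**Conclusion.** The point holds firmly for primary endpoint 1. As worded, it includes lesions formed on identical treatment and so weakens the withdrawal contrast. In a yes/no analysis the risk difference shrinks by the factor (1 − shared prevalence at month 6), if new-lesion risk applies equally to those without prior lesions. For GFR and rejection the finding is narrower: no origin or month-6 baseline is named for goal 2, and dilution follows only if early values or events are pooled.

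The loss cannot be sized from the document. Under the assumed lesion rates, power is about 51 to 30% against 64 to 54%. The second range describes a simple lesion-free subset, used here to show the scale; it is not the analysis recommended below. All figures take 90 per maintenance strategy and ignore Group 3 and 4 subjects who never convert, who would reduce the contrast under either definition. The change is worth making, but the present wording does not invalidate the trial.

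**What to change.** For the withdrawal contrast only, compare Groups 3+4 with Groups 1+2 as randomised, whether or not conversion took place:

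- **Endpoint 1:** new or progressed Banff nephropathy after the month-6 biopsy, adjusted for the month-6 grade and not restricted to lesion-free subjects.
- **Endpoint 2:** month-12 and month-24 renal function, adjusted for the month-6 value.
- **Rejection and graft loss:** counted from a month-6 landmark common to all four groups, with the from-transplant analysis as a sensitivity analysis.

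Keep transplant as time zero for single versus divided rATG.

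Treatment and data collection do not change. The cost is that subjects who die or lose the graft before month 6, or who lack a month-6 biopsy (the protocol allows it to be forgone), contribute less to this contrast. Redefining a primary endpoint after two interim analyses, one of them published, is also a substantive change. It should be documented as made after those analyses and before the withdrawal-phase analysis, whose timing is still open.
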